## Abstract

**Background:**

High risk prescribing can compromise independent wellbeing and quality of life in older adults. The aims of this project are to determine the prevalence, risk factors, clinical consequences, and costs of high risk prescribing, and to assess the impact of interventions on high risk prescribing in older people.

**Methods:**

The proposed project will utilise data from the 45 and Up Study, a large scale cohort of 267,153 men and women aged 45 and over recruited during 2006–2009 from the state of New South Wales, Australia linked to a range of administrative health datasets. High risk prescribing will be assessed using three indicators: polypharmacy (use of five or more medicines); Beers Criteria (an explicit measure of potentially inappropriate medication use); and Drug Burden Index (a pharmacologic dose-dependent measure of cumulative exposure to anticholinergic and sedative medicines). Individual risk factors from the 45 and Up Study questionnaire, and health system characteristics from health datasets that are associated with the likelihood of high risk prescribing will be identified. The main outcome measures will include hospitalisation (first admission to hospital, total days in hospital, cause-specific hospitalisation); admission to institutionalised care; all-cause mortality, and, where possible, cause-specific mortality. Economic costs to the health care system and implications of high risk prescribing will be also investigated. In addition, changes in high risk prescribing will be evaluated in relation to certain routine medicines-related interventions. The statistical analysis will be conducted using standard pharmaco-epidemiological methods including descriptive analysis, univariate and multivariate regression analysis, controlling for relevant confounding factors, using a number of different approaches.

**Discussion:**

The availability of large-scale data is useful to identify opportunities for improving prescribing, and health in older adults. The size of the 45 and Up Study, along with linkage to health databases provides an important opportunity to investigate the relationship between high risk prescribing and adverse outcomes in a real-world population of older adults.

## Background

In older adults, high risk prescribing can be defined as prescribing likely to lead to adverse clinical outcomes or prescribing that does not align with quality use of medicines principles. A range of indicators have been proposed to quantify high risk prescribing in older people. These include multiple medication use or polypharmacy, potentially inappropriate prescribing and exposure to high risk medicines, measured using different risk assessment tools.

Although the concomitant use of multiple medicines is often indicated in the treatment and prevention of health problems, polypharmacy is generally considered as high risk prescribing in older adults, and is associated with increased risk of harm [1-3], including adverse drug reactions, falls, hospitalisation, institutionalisation, and mortality [1]. Polypharmacy (concomitant use of ≥ 5 medicines) is common in older adults, and is estimated to be present in around half of Australians aged 65–74 years, and two-thirds of those aged ≥75 years [4]. The prevalence of “hyperpolypharmacy” (concomitant use of ≥ 10 medicines) in community-dwelling older adults has been reported to range from 5% to 26% [5,6].

High risk prescribing also includes potentially inappropriate prescribing, defined as the use of medicines whose potential harms to older adults may outweigh the benefits [7]. Potentially inappropriate prescribing can be assessed using explicit and implicit approaches. The Beers Criteria, an explicit USA consensus list is the most widely used indicator to define potentially inappropriate prescribing [7,8]. The associations between Beers Criteria and outcomes have been investigated across a range of populations and settings of older adults, with mixed findings being reported across studies [9]. Despite the efforts to improve the quality use of medicines in this population, recent systematic review suggests that potentially inappropriate prescribing is still common in older people [10].

High risk prescribing may also encompass exposure to “high-risk” medicines such as those with anticholinergic and sedative properties. A number of anticholinergic and/or sedative scores have been developed to capture the cumulative exposure to these pharmacological classes [2]. One such tool is the Drug Burden Index (DBI), a pharmacological score based on the principles of dose–response and cumulative effect, that measures an individual’s total exposure to medicines with anticholinergic and sedative effects [11]. In studies of older people, the prevalence of exposure to DBI medicines ranged from 29–70% [12,13]. Increasing DBI score has been associated with a higher risk of a range of adverse clinical outcomes, including functional impairment, frailty, falls and hospitalisation in populations of older adults from the USA, Australia and Europe [11-19].

Strategies to reduce high risk prescribing, including pharmacist-conducted medication reviews, educational interventions and policy approaches, have been trialled in older adults [20-22]. However, the success of these interventions has been limited. To reduce the likelihood of clinically significant adverse outcomes, rational withdrawal of medications may be the appropriate clinical decision and may result in significant clinical benefits in some older people with high risk prescribing [23]. To date, real-world approaches to reduce polypharmacy in older people have generally not been successful [22,24]. While interventional approaches can reduce medication exposure in older adults, the evidence for their clinical effectiveness and sustainability is conflicting [24].

The current evidence from pharmaco-epidemiological studies suggests that high risk prescribing increases the risk of adverse outcomes in older adults [1,2]. However, there is a lack of reliable evidence at the population level on the prevalence and outcomes relating to high risk prescribing in older people. Moreover, evidence is required regarding the impact of pragmatic medicines-related interventions aimed at improving medication management in older adults. The aims of this project are to determine the prevalence, risk factors, clinical implications and costs of high risk prescribing, and the impact of interventions on high risk prescribing in older people within a large population-based cohort study; specifically to:

1) Estimate the prevalence of high risk prescribing;

2) Investigate the risk factors for high risk prescribing;

3) Quantify the relationship of high risk prescribing to adverse health outcomes;

4) Determine whether associations between high risk prescribing and adverse outcomes vary according to individual and/or health care system specific factors;

5) Calculate the economic cost and implications of high risk prescribing to the health care system;

6) Investigate whether certain routine medicines-related interventions, including the Home Medicines Review and Chronic Disease Management are associated with reductions in high risk prescribing.

## Methods

### Overview of data sources

The proposed cohort analysis will utilise a population-based dataset combining self-reported questionnaire data (including data on life-style and social factors, functional capacity, physical activity, medical diagnosis and medication data) linked to routine administrative health datasets. This project will utilise the following data sources: the 45 and Up Study baseline questionnaire; the Australian Commonwealth Medicare Benefit Scheme (MBS) claims data, Pharmaceutical Benefit Scheme (PBS) claims data, Aged and Community Care Management Information System (ACCMIS) database, National Death Index; and New South Wales (NSW) datasets including the Admitted Patients Data Collection (APDC), and the Register of Births, Deaths and Marriages (Figure 1).

**Figure 1 F1:**
[figure not shown]
**Overview of the data sources. **Abbreviation: ABS, Australian Bureau of Statistics; NSW, New South Wales.

### The 45 and Up study cohort

The 45 and Up Study cohort includes 267,153 men and women aged 45 and over from the state of NSW, Australia, randomly sampled from the Medicare Australia database [25]. Participants completed a self-administered postal questionnaire and provided signed consent for participation and follow-up, including linkage to health records (including data on deaths, hospital admissions, and aged care admissions). Recruitment was conducted from February 2006 to April 2009, with an 18% response rate. Following exclusion of individuals with missing data on age and sex, 266,074 participants remained. Of these, 143,199 (54%) are aged 60 years and over (Table 1). Overall, 28% (n = 73,528) of the cohort reported holding a healthcare concession card, hereafter referred as concession card holders. This status will also be confirmed using the health administrative databases. For the purposes of the High Risk Prescribing project, the study sample will be restricted to cohort members who are concession card holders, as this allows full capture of health care utilisation.

**Table 1 T1:** Characteristics of the concession card holders in the 45 and Up study, and total study population

**Characteristic**^ **~** ^	**Concession card holders (n = 73,528; 28%)**	**All participants (n = 266,074)**
** *Socio-demographic factors* **		
Age groups, n (%)		
45–59 years	14,888 (20%)	122,875 (46%)
60–69 years	25,599 (35%)	73,833 (28%)
70–79 years	20,432 (28%)	42,256 (16%)
≥ 80 years	12,609 (17%)	27,098 (10%)
Sex, n (%)		
Male	32,755 (45%)	123,402 (46%)
Female	40,773 (55%)	142,672 (54%)
Country of birth, n (%)		
Australia born	54,031 (73%)	199,342 (75%)
Born outside of Australia	19,497 (27%)	66,732 (25%)
Highest educational qualification, n (%)		
University degree	7,289 (10%)	61,290 (23%)
Certificate/diploma	21,932 (30%)	84,556 (32%)
Higher school/leaving certificate	6,757 (9%)	25,985 (10%)
School/intermediate certificate	20,338 (28%)	58, 611 (22%)
No certificate	15,358 (21%)	31,194 (12%)
Household income, n (%)		
Less than $20,000	31,380 (43)	52,359 (20%)
$20,000-$39,999	17, 260 (23%)	46,555 (17%)
$40,000-$69,999	5,545 (8%)	46,968 (18%)
$70,000 or more	1,007 (1%)	62,553 (24%)
Missing	18,336 (5%)	57,639 (22%)
Marital status, n (%)		
Married/defacto	46,771 (64%)	198,760 (75%)
Not married^*^	26,265 (36%)	65,703 (25%)
Region, n (%)		
Inner regional	29,909 (38%)	93,581 (35%)
Major cities	28,600 (39%)	119,792 (45%)
More remote	17,008 (23%)	52,640 (20%)
** *Lifestyle and social factors* **		
Alcohol use, number of drinks per week, n (%)		
None	31,163 (42%)	86,198 (32%)
1–14	31,400 (43%)	136,880 (51%)
≥ 15	8,517 (12%)	37,357 (14%)
Smoking history, n (%)		
Current smoker	6,833 (9%)	19,247 (7%)
Former smoker	28,365 (39%)	96,080 (36%)
Never-smoker	38,017 (52%)	149,900 (56%)
Body Mass Index, kg/m^2^, n (%)^#^		
Underweight (15–18.4 kg/m^2^),	1,139 (2%)	3,094 (1%)
Normal weight (18.5–24.9 kg/m^2^)	23,306 (32%)	90,563 (34%)
Overweight (25.0–29.9 kg/m^2^)	25,624 (35%)	97,163 (37%)
Obese (≥30.0 kg/m^2^)	16,761 (23%)	54,903 (21%)
Missing	6,698 (9%)	20, 351 (8%)
** *Functional capacity and medical diseases* **		
Needing assistance with daily tasks because of long-term illness or disability, n (%)		
Yes	8,113 (11%)	14,499 (5%)
No	60,529 (82%)	238,661 (90%)
Missing	4,886 (7%)	12,914 (5%)
Physical activity, tertile, n (%)		
1	22,087 (30%)	77,019 (29%)
2	23,422 (32%)	86,501 (33%)
3	21,986 (30%)	87,411 (33%)
Missing	6,033 (8%)	15,143 (6%)
Self-rated health, n (%)		
Excellent	5,705 (8%)	38,758 (15%)
Very good	20,449 (28%)	94,776 (36%)
Good	26,822 (36%)	86,711 (33%)
Fair	13,864 (19%)	30,822 (12%)
Poor	3,187 (4%)	5,625 (2%)
Missing	3,501 (5%)	9,328 (4%)
Kessler 10 score, psychological distress, n (%)		
Low	42,596 (58%)	180,524 (68%)
Moderate	10,223 (14%)	36,817 (14%)
High	4,623 (6%)	12,718 (5%)
Very high	2,427 (3%)	5,144 (2%)
Missing	13,659 (19%)	30,871 (12%)
Diabetes, n (%)		
Yes	10,716 (85%)	24,609 (9%)
No	62,812 (5%)	241,465 (91%)
Cardiovascular diseases, n (%)^^^		
Yes	17,157 (23%)	39, 815 (15%)
No	56,371 (77%)	226,259 (85%)
Cancer, n (%)^≠^		
Yes	11,258 (15%)	30,426 (11%)
No	62,270 (85%)	235,648 (89%)

Missing values given where they amount to 5% or more of the total.

^**~**^ Percentages do not add up to 100% in all instances due to missing values and rounding.

^*^Single, widowed or divorced.

^#^Body Mass Index categories in line with World Health Organization classifications.

^^^Heart disease, stroke or blood clot.

^≠^Self-reported history of cancer excluding skin cancer.

### Commonwealth administrative health datasets

#### MBS and PBS administrative databases

MBS and PBS are part of the Australia's national health insurance arrangements [26]. These schemes provide subsidised access to medical services and pharmaceuticals for Australian residents. The MBS database contains detailed information on Commonwealth subsidised claims for medical services performed outside the public hospital inpatient setting.

The PBS database contains information on Commonwealth subsidised claims for prescribed medicines listed on the Schedule of Pharmaceutical Benefits. There are two main groups of PBS beneficiaries, concession card holders and general beneficiaries. The PBS database records only PBS-listed prescription medicines that attract a government subsidy. Concession card holders are required to contribute a co-payment of $5.80 (as at January 1^st^ 2012) towards the cost of their medicines. Since all PBS medicines cost more than the concession card holder threshold, they will always attract a Commonwealth subsidy. Therefore medication data from concession card holders are captured consistently in the PBS database. However, the co-payment threshold for general beneficiaries is $35.40 (as at January 1^st^ 2012). There are a range of PBS-listed medicines that cost less than this co-payment threshold. When these medicines are dispensed to a general beneficiary, the general beneficiary is required to pay the full cost of the medicines and the government does not contribute to payment. Consequently, PBS-medicines falling below the co-payment were not captured in the PBS database for general beneficiaries. However, following a policy change, since April 2012 the PBS database now captures all PBS-dispensed medicines, regardless of whether the government contributes to the payment. To manage the potential incomplete capture of PBS-listed medicines dispensed to general beneficiaries we will restrict our analysis to healthcare concession card holders. Recent estimates indicate that over 90% of individuals aged 65 years and over hold a government health care concession card [27]. Therefore, the results will be highly generalisable to the general population of older Australians.

#### ACCMIS, National Death Index and Australian bureau statistics mortality data

The ACCMIS contains information on residential aged care services provided to older people who can no longer live at home [28]. The National Death Index dataset contains records of all deaths occurring in Australia since 1980 [29], along with data from the Australian Bureau of Statistics on cause of death.

### NSW health administrative datasets

#### APDC and NSW registry of births and death databases

The APDC is a complete census of all services for admitted patients provided by public hospitals, public psychiatric hospitals, public multi-purpose services, private hospitals and private day procedure centres in NSW, Australia [30]. Finally, the NSW Registry of Births and Death will be utilised to provide fact of death data.

### Linkage process

The data linkage procedures will be performed separately for Commonwealth and NSW databases as these health datasets are held by different jurisdictions. The linkage processes are summarised below.

#### Commonwealth datasets

As 45 and Up Study participants were sampled from the Medicare enrolment database and each was assigned an encrypted version of the unique Medicare ID, the linkage to PBS and MBS Commonwealth data is deterministic. PBS and MBS data for all 45 and Up Study participants have already been linked to baseline questionnaire data. The linkage with the National Death Index dataset, including the Australian Bureau of Statistics mortality data will be performed by the Australian Institute of Health and Welfare. Linkage of the ACCMIS database to the 45 and Up Study and other datasets through a third party using best practice privacy preserving protocols will be explored.

#### NSW datasets

The Centre for Health Record Linkage (CHeReL) routinely links identifying details (including full name, date of birth, sex and address) from 45 and Up Study participants to those from the NSW APDC and death records, to provide regular updates to events in the cohort. This is a part of an established program of linkage. Records are matched probabilistically using privacy-preserving current best practice with *ChoiceMaker* software [31], an algorithm based on maximum entropy theory to develop a predictive model that classifies record pairs.

### Medication exposure

Medication exposure will be measured using the 45 and Up Study predominantly using PBS dispensing data, validated and calibrated against self-reported medication use from the 45 and Up Study questionnaire. As the PBS database does not capture private prescriptions, medicines dispensed to public hospital inpatients, over-the-counter medicines and many complementary and alternative medicines, the extent to which PBS data reliably categorise high risk prescribing is not known. The authors are currently conducting the validation projects to estimate the extent and implications of any under-ascertainment of high risk prescribing using PBS data, compared with self-reported measures from the 45 and Up baseline questionnaire.

#### Assessment of high risk prescribing

High risk prescribing will be defined using three indicators: polypharmacy; Beers Criteria; and DBI. Polypharmacy will be defined as the concurrent dispensing of five or more medicines [32] over a six month period, and using the total number of medicines as a continuous variable. The updated 2010 Beers criteria will be used to assess potentially inappropriate prescribing [8]. The linked datasets will be screened for medicines and diagnosis considered by the updated Beers criteria. Data on six medical conditions included in the updated Beers criteria have been collected for the 45 and Up Cohort. Medicines will be used as a surrogate marker of other diseases considered by the updated Beers criteria [15]. Inappropriate prescribing will be considered present if the participant is prescribed at least one medicine included in the updated Beers criteria.

The DBI, a measure of exposure to drugs with anticholinergic or sedative effects will be calculated using the equation [11],

(1)$$\text{DBI}=\sum \left[D/\left(\delta +D\right)\right],$$

where *D* is the daily dose, and *δ* is the minimum efficacious dose (the minimum dose in the approved product information registered by the Australia’s Therapeutic Goods Administration, TGA), an estimate of the dose required to obtain 50% of the maximal effect. The daily dose will be estimated from the total quantity dispensed, using a standard pharmaco-epidemiological approach [33], by multiplying the strength (mg) and quantity dispensed, divided by the time period over which the medicines were taken during the study period. The total drug burden for the participant will be calculated as the sum of the drug burden of all anticholinergic or sedative medicines a participant is exposed to using a linear additive model. The Anatomical Therapeutic Codes (ATC) will be used to screen for anticholinergic and sedative drugs [34]. The minimum dose registered by the TGA will be obtained for all drugs with anticholinergic and sedative effects.

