### Sample size

Using data available to the end of 2012, the project will be highly powered for the main outcomes, with the ability to detect a minimum relative risk of death (the least common outcome) of 1.12, for each of the three high risk prescribing indices (assuming the following prevalences: DBI 48%; Beers 20% and polypharmacy 30%) [5,15], at 5% significance and 80% power. The incidence of total hospitalisation and hospitalisation for falls and fractures will be greater than the incidence of death, and hospitalisation for adverse drug reactions is similar to the incidence of death. To investigate the relationship between MBS interventions and outcomes, the linkage will be updated annually to increase power. An estimated 5% of people aged ≥ 65 have had a Home Medicines Review; however we are not able to locate estimates for other MBS review items. Assuming 5% exposure over the study period, for the smallest high risk prescribing stratum (Beers: 20%) this would allow detection of a relative change in prevalence of 0.05, comparing *before* and *after* the intervention.

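### The Beers scoring rule counts any listed medicine as inappropriate prescribing and states no diagnosis condition, although the same section screens for diagnoses

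*Protocol article*

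**What the plan says.** Four consecutive sentences under Assessment of high risk prescribing define the Beers indicator.

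- What is screened: "The linked datasets will be screened for medicines and diagnosis considered by the updated Beers criteria".
- Which diagnoses are held directly: "Data on six medical conditions included in the updated Beers criteria have been collected for the 45 and Up Cohort".
- How the rest are obtained: "Medicines will be used as a surrogate marker of other diseases considered by the updated Beers criteria".
- When the indicator is positive: "Inappropriate prescribing will be considered present if the participant is prescribed at least one medicine included in the updated Beers criteria".

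The Statistical analysis section says the three indicators will be calculated from the cohort linked to PBS data, restricted to concession card holders. Other sources are brought in afterwards for admissions, deaths and institutionalisation. The Sample size section plans on "assuming the following prevalences: DBI 48%; Beers 20% and polypharmacy 30" per cent, and on "the ability to detect a minimum relative risk of death (the least common outcome) of 1.12, for each of the three high risk prescribing indices". It does not say whether the 20% for Beers includes items that depend on a diagnosis.

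**The concern.** The first three sentences treat diagnosis as part of the criteria: conditions are collected, and where they were not collected a surrogate is found. The fourth sentence makes the indicator depend on medicines alone. Two competent analysts could follow this section and build different exposure variables. One would flag everyone with a listed medicine. The other would flag a disease-dependent medicine only when the disease is also present.

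Beers is one of three exposure definitions. It is used for prevalence, for risk factors, for the relation to admission and death, for the cost comparison (which is run on each definition) and for the before-and-after intervention analysis, where it is the smallest stratum. A medicine-only flag is also likely to track the number of medicines taken, which is already measured by the polypharmacy indicator.

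**Working it through.** **1. The rule against the screening.** Take a medicine that the criteria list only for people with disease X.

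| Participant | Sentence as written | Rule using the screened diagnoses |
|---|---|---|
| Takes the medicine, has X | positive | positive |
| Takes the medicine, does not have X | positive | negative |
| Does not take the medicine | negative | negative |

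The rules differ only in the second row. Under the sentence as written, no diagnosis changes anyone's status, so the screening step has no effect. Everyone positive under the diagnosis-based rule is also positive under the literal rule. Literal prevalence can therefore only be equal or higher.

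**2. The plan's own figure.** The article gives no number for the second row, so there is none to reproduce on this point. The nearest figure is the detectable relative risk of death of 1.12. With 20% exposed, two-sided 5% (sidedness assumed) and 80% power, the Schoenfeld formula gives

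deaths = (1.960 + 0.842)² / [0.20 × 0.80 × (ln 1.12)²] = 3,820,

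which is 3,820 / 73,528 = 5.2% of the concession card holders. The article states no death rate, so 1.12 can be back-solved but not confirmed.

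**3. Illustration only.** Let f be the share of flagged participants who lack the qualifying disease. The article does not give f, so every value here is assumed. Hold 20% flagged and 3,820 deaths, and suppose the wrongly flagged carry no excess risk. Then

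observed RR = (1 − f) × 1.12 + f × 1,

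prevalence with a criterion truly met = 0.20 × (1 − f).

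| f (assumed) | Criterion truly met | Observed RR, literal rule | Power, literal rule | Power, diagnosis-based rule |
|---|---|---|---|---|
| 0% | 20% | 1.120 | 80% | 80% |
| 10% | 18% | 1.108 | 72% | 77% |
| 20% | 16% | 1.096 | 62% | 73% |
| 30% | 14% | 1.084 | 51% | 68% |
| 50% | 10% | 1.060 | 30% | 56% |

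The last column shows that part of the power loss comes from there being fewer truly exposed people. The cost of misclassification is the gap between the last two columns.

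**4. Why the direction is not settled.** The dilution in step 3 follows from giving the wrongly flagged baseline risk. Suppose instead that they are sicker. Take f = 20% and an assumed relative risk of 1.50 for them, with 1.12 for the truly exposed, both against people flagged under neither rule.

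- Literal rule: 0.80 × 1.12 + 0.20 × 1.50 = 1.196.
- Diagnosis-based rule: the wrongly flagged 4% (0.20 × 20%) join the 80% in the reference group, whose relative risk becomes (0.80 + 0.04 × 1.50) / 0.84 = 1.024. The observed RR is 1.12 / 1.024 = 1.094.

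Here the literal rule inflates the association.

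**5. Which prevalence the 20% is.** If the planned 20% is the diagnosis-based prevalence, the literal rule would measure 0.20 + 0.80x, where x is the share of the remaining 80% who are wrongly flagged. If 20% is already the flagged prevalence, step 3 applies. The article does not say which it is.

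**The case against.** The strongest reply is that the scoring sentence should be read with the three before it. Those sentences serve no purpose unless diagnoses are used, so the last one may simply mean that, after screening, one qualifying medicine is enough. This reading is plausible and it stands. The article does not say that diagnoses are ignored, and a fuller item list may exist elsewhere. It does not rescue the wording, however: the sentence refers to a medicine included in the criteria, not to a criterion being met, and nothing else in the article says how diagnoses enter the score.

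Three stronger conclusions are tempting, and the article does not support them.

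- **That people without the disease will in fact be counted as exposed.** This follows only if the sentence is applied literally.
- **That prevalence is overstated and associations are diluted.** Literal prevalence cannot be below the diagnosis-based one, but the Medication exposure section also describes under-capture by PBS data, which works the other way. For associations, the direction depends on the risk of those wrongly flagged, as shown in the working.
- **That missing diagnoses will come from medicines alone.** The article does not say so. The linked datasets to be screened may include the hospital admissions collection, although the Statistical analysis section mentions only the cohort linked to PBS data when the indicators are calculated.

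**Conclusion.** The scoring sentence is wrong as written. Followed literally, it classes as exposed people who lack the disease on which a listing depends, and it leaves the diagnosis screening unused. This rests on the article's own indication that the criteria take account of diagnoses. It needs no outside knowledge of the list.

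The size cannot be determined from the article. The illustrated fall in observed relative risk from 1.12 to between 1.108 and 1.060 depends on an assumed 10% to 50% of flagged participants lacking the disease and on their carrying no excess risk. With a different assumption about their risk the association is inflated. The definition should be corrected because it enters every main analysis and a target as small as 1.12 leaves little room for an exposure that analysts may build in two ways.

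**What to change.** Replace the scoring sentence with:

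> *Inappropriate prescribing is present if the participant meets at least one updated Beers criterion: a medicine listed irrespective of diagnosis, or a medicine listed for a disease or condition together with evidence of that disease (questionnaire, prior diagnoses in the linked hospital data, or a medicine surrogate where neither covers the condition).*

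If the diagnosis-based rule was always intended, this only corrects the wording. If not, it needs a little more programming on data already in the study: the plan already links hospital admissions and needs their causes for falls and fractures. Measured prevalence may come out lower than under the literal rule. The Sample size section should then say which definition its 20% refers to.
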